# SAFETY REPORTING

## Section 10 WMO event

In accordance to section 10, subsection 1, of the WMO, the investigator will inform the subjects and the reviewing accredited METC if anything occurs, on the basis of which it appears that the disadvantages of participation may be significantly greater than was foreseen in the research proposal. The study will be suspended pending further review by the accredited METC, except insofar as suspension would jeopardise the subjects’ health. The investigator will take care that all subjects are kept informed.

## Adverse and serious adverse events

Adverse events are defined as any undesirable experience occurring to a subject during the study, potentially related to the intervention programme or study measures. All adverse events reported spontaneously by the subject or observed by the investiga­tor or his staff will be recorded in an electronic database.

A serious adverse event is any untoward medical occurrence or effect that at any dose results in death;

- is life threatening (at the time of the event);
- requires hospitalisation or prolongation of existing inpatients’ hospitalisation;
- results in persistent or significant disability or incapacity;
- is a new event of the trial likely to affect the safety of the subjects, such as an unexpected outcome of an adverse reaction, lack of efficacy of an IMP used for the treatment of a life threatening disease, major safety finding from a newly completed animal study, etc.

SAEs will be reported at the end of the study to the accredited METC that approved the protocol. However, SAEs that result in death or are life threatening will be reported expedited through the webportal Toetsingonline. The expedited reporting will occur not later than 7 days after the responsible investigator has first knowledge of the adverse reaction. This is for a preliminary report with another 8 days for completion of the report.

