- Goal-setting: participants will be instructed to set specific (i.e. quantifiable) behavioral goals for the timeframe until the next session. The goals should be realistic, yet moderately challenging.
- Stimulus control: participants must identify stimuli and high risk-situations. They should develop their own controlling strategies, such as learning to shop carefully for healthy food, keeping high-calorie foods out of the house, limiting the times and places of eating, and consciously avoiding situations in which overeating occurs.
- Problem solving: participants should identify and self-correct problem areas related to their eating
- Relapse prevention: several skills to overcome setbacks and to cope with problems will be taught.

*Mode of delivery:*

The weight loss intervention is delivered by dieticians experienced in overweight treatment. Individual and group sessions are planned. Group sessions are supposed to provide a combination of social support and a healthy dose of competition. Group treatment is also more cost-effective than individual care60. Furthermore, there is evidence that group support might produce greater weight loss effects than individual counselling alone61. A family member or other support person may be invited to attend any or all sessions to increase social support62, 63.

*Intensity and duration of contacts:*

Frequent contact between participants and team members is proven to be a relevant success factor for weight reduction64. In most studies65 lifestyle modification training is provided weekly for an initial period of 16 weeks. In our programme, the contact frequency will be quite similar (see Figure 1). The dietary intervention will consist of 2 one-hour individual sessions, 5 one-hour group sessions and 7 phone calls. A recently published large randomised controlled trial in overweight adults showed that with this kind of dietary intervention relevant weight loss can be achieved. This study found an average weight loss of 7% of initial weight after six months66.

*Group sessions:*

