## Waiting list control group (group C)

Participants in the waiting list control are requested to retain body weight according to the isocaloric diet and to maintain their habitual exercise pattern. We will give very clear recommendations on this throughout the study. Potential changes in weight, exercise and eating pattern will be monitored by four phone calls by the researchers or dietician (See figure 1). After completion of the 5 month study period, the control participants will be provided with all study materials of the diet and exercise programme. Additionally, we will offer them four dietary weight loss group sessions and three exercise group sessions (including one exercise education session).

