## Follow-up of adverse events

In case of non-attendance to sports classes, dietary (group) sessions or planned visits to the hospital the reasons for absence will be checked (by dietician/physiotherapist) and be reported to the researchers.

All participants are asked to report unplanned hospitalisation during the study period; this will also be checked at the end of the study.

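### Non-serious adverse events are filtered by suspected cause and detected through very unequal contact, so their rates will not be comparable between arms

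*Protocol*

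**What the plan says.** **Definition.** Section 6.2 of the protocol states: "Adverse events are defined as any undesirable experience occurring to a subject during the study, potentially related to the intervention programme or study measures". It does not say who judges relatedness. For serious events the same section has no such limit: "A serious adverse event is any untoward medical occurrence or effect that at any dose results in death", followed by the other seriousness criteria.

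**Collection.** Section 6.2 records "All adverse events reported spontaneously by the subject or observed by the" investigator or staff. No scheduled adverse event question appears in section 6 or in Figure 1. Section 6.3 adds two active steps. The first is tied to attendance: "In case of non-attendance to sports classes, dietary (group) sessions or planned visits to the hospital the reasons for absence will be checked". The second covers every arm: "All participants are asked to report unplanned hospitalisation during the study period; this will also be checked at the end of the study".

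**Contact.** For D, section 3.2 says: "The dietary intervention will consist of 2 one-hour individual sessions, 5 one-hour group sessions and 7 phone calls". Section 3.3 gives E two individual dietary sessions, seven calls and supervised exercise twice a week for 14 weeks. For C, section 3.4 says that changes in weight, exercise and eating "will be monitored by four phone calls by the researchers or dietician".

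**Use of the data.** Section 7 plans no comparison of adverse events by arm. The Summary names exercise injury as one of the burdens of taking part.

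**The concern.** Two features act in the same direction.

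1. An experience thought unrelated to the programme or a measurement is not an adverse event and need not be recorded. Women in C have no exercise or weight-loss programme during the study. The same back or knee complaint can easily be linked to the programme in E, less easily in D, and hardly at all in C unless a measurement is blamed.
2. Detection depends on the woman volunteering the event or a staff member noticing it, and the opportunity for either differs several-fold between arms. The attendance check widens the gap, because only E and D have sessions to miss.

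At stake is the reading of any safety table. E against D is the central comparison of the trial, and injury is the expected cost of adding exercise. Most such injuries would probably be non-serious, which is the class affected. Events never recorded cannot be recovered by a later analysis plan.

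There is also an inconsistency within section 6.2: an unrelated hospitalisation meets the SAE definition but not the AE definition, so SAEs are not a subset of AEs.

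**Working it through.** **Step 1. Check the stated call counts against Figure 1 (weeks 6 to 21).**

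| Item | Text | Figure 1 |
|---|---|---|
| Calls, D and E | 7 (sections 3.2, 3.3) | 7 (weeks 8, 10, 12, 14, 16, 18, 20) |
| Group sessions, D | 5 (section 3.2) | 5 (weeks 7, 9, 11, 15, 19) |
| Calls, C | 4 (section 3.4) | 3 (weeks 6, 10, 20); 5 if run-in weeks 2 and 4 are added |

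The D and E counts reproduce. The C count does not: neither 3 nor 5 equals 4.

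**Step 2. Total scheduled contacts after randomisation,** counting the week-21 measurement visit once in every arm.

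- E: 14 × 2 = 28 classes, + 2 individual sessions + 7 calls + 1 visit = 38. This is a minimum, because section 3.3 also promises supervised walking groups without giving their number.
- D: 5 group + 2 individual + 7 calls + 1 visit = 15.
- C: 3 calls + 1 visit = 4 by Figure 1, or 4 calls + 1 visit = 5 by section 3.4.

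Ratios: E:C is 38/4 = 9.5 or 38/5 = 7.6; D:C is 15/4 = 3.75 or 15/5 = 3.0.

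**Step 3. What this could do to recorded rates.** The protocol gives no chance of mention and no recall period, so everything below is assumption. Suppose the true risk is the same in all arms, an event is equally likely to fall before any of the k contacts, it is remembered to the end, and each later contact brings it out with chance d. The expected share captured is

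(1/k) × Σ over j = 1 to k of [1 − (1 − d)^j] = 1 − (1 − d)[1 − (1 − d)^k]/(k·d).

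Example, d = 0.10 and k = 4: 1 − 0.9 × (1 − 0.6561)/0.4 = 0.226.

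| d | E (38) | D (15) | C (4) | C (5) | E:C with 4 | E:C with 5 |
|---|---|---|---|---|---|---|
| 0.02 | 30.9% | 14.6% | 4.9% | 5.8% | 6.3 | 5.3 |
| 0.10 | 76.7% | 52.4% | 22.6% | 26.3% | 3.4 | 2.9 |
| 0.30 | 93.9% | 84.5% | 55.7% | 61.2% | 1.7 | 1.5 |

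E:D over the same rows is 2.1, 1.5 and 1.1.

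**Step 4. Two changes of assumption.**

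- *Short recall.* If events are forgotten after 4 weeks and d is 0.10 to 0.30, a simulation with event times uniform over weeks 6 to 21 captures 57 to 90% in E and 8 to 22% in C (4 contacts). The E:C ratio is then about 57/8 = 7.1 down to 90/22 = 4.1.
- *A searching final visit.* If the week-21 visit alone brings out 70% of remembered events, the bracket in the formula becomes 1 − 0.3 × (1 − d)^(j − 1). Capture in E and C (4 contacts) is 78.8% and 70.9% at d = 0.02, 92.2% and 74.2% at d = 0.10, and 97.4% and 81.0% at d = 0.30. The E:C ratio is 1.1 to 1.2.

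In every scenario E exceeds C. All of these figures come before the relatedness filter.

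**The case against.** The strongest reply is that no harm comparison is planned. Safety is neither an objective nor an endpoint, and section 7 does not analyse it. Serious events carry no relatedness limit, and every participant is asked to report unplanned hospitalisation, with a further check at the end. The week-21 visit includes history taking and physical examination (Summary), and medication use is asked at measurement visits (section 5.3), so it may find much of what the calls miss.

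Much of this stands. It confines the point to non-serious events and to any table or judgement later built on them, and it shows that the size of the bias is not established. It does not remove the point: the final visit carries no stated adverse event question, and the definition would still exclude what is judged unrelated.

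Three stronger readings are tempting, and the documents do not support them.

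- *That all harm rates by arm must be wrong.* Serious events and hospitalisation are covered in every arm, as above.
- *That the control count is near zero by definition.* The definition includes events related to study measures, and controls undergo blood sampling, DEXA, MRI and the maximal exercise test.
- *That section 6.1 cannot work without a control background rate.* Its yardstick is what the research proposal foresaw, not the control arm.

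It also cannot be said that relatedness is judged by someone who knows the arm, because no assessor is named. Nor is collection purely spontaneous, since staff observation counts and the absence check includes hospital visits, which C has.

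**Conclusion.** The point holds for non-serious adverse events. Recording is conditional on suspected relatedness, and detection runs through at least 38, 15 and 4 or 5 scheduled contacts in E, D and C. Rates by arm would not be comparable if tabulated, and the bias is towards more recorded events in E.

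The contact counts rest on the protocol alone. The effect on rates does not: with equal true risk, the spurious E:C ratio ranges from about 1.1 (searching final visit, full recall) to about 7 (four-week recall, 10% chance of mention per contact), and nothing in the protocol chooses between them.

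Two internal inconsistencies need no assumption. SAEs as defined are not a subset of AEs, and the four control calls in section 3.4 do not match the three after randomisation in Figure 1.

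The change is worth making because it is cheap and because the lost information cannot be restored later.

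**What to change.** 1. In section 6.2, define an adverse event as any undesirable experience during the study, whatever the suspected cause. Keep the present time span: starting at randomisation would drop events from the run-in and from the week-5 baseline measurements, including the maximal exercise test.
2. Record relatedness as a separate field, and word the SAE definition so that every SAE is also an AE.
3. In section 6.3, put one identical scripted question (injury, new complaint, doctor visit, hospitalisation) to all three arms at contacts they already share: the week-10 call, the week-20 call and the week-21 visit. That gives 3, 3 and 3 scheduled enquiries after randomisation.
4. Base any between-arm table on those answers. List spontaneously reported and class-observed events separately.
5. Reconcile the number of control calls in section 3.4 with Figure 1.

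The cost is revised wording in sections 6.2 and 6.3 and one question at three existing contacts. More minor unrelated events will be recorded, and events between contacts will depend partly on recall. No new visits or staff are needed.

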## Follow-up of adverse events

In case of non-attendance to sports classes, dietary (group) sessions or planned visits to the hospital the reasons for absence will be checked (by dietician/physiotherapist) and be reported to the researchers.

All participants are asked to report unplanned hospitalisation during the study period; this will also be checked at the end of the study.

# STATISTICAL ANALYSIS

## Descriptive statistics

Baseline demographics and characteristics will be reported by treatment group descriptively. Means and SDs will be presented for continuous normally distributed variables and medians and ranges for non-normally distributed variables. Categorical variables will be presented by frequencies per group (absolute numbers and percentages).

Baseline and end of study values of sex hormone levels, total body fat and intra-abdominal body fat will be tabulated by treatment group. If sex hormone levels are non-normally distributed, these will be log transformed and geometric means will be presented.

## Analysis

Our primary and secondary endpoints will be changes in sex steroid hormones, body composition and fitness during the study. If sex hormones are non-normally distributed, log transformations will be used for analyses. We will analyse the effects by linear regression analysis. We will compare the effects of the diet group versus the exercise group, the diet versus control, and exercise versus control. The main analysis will be performed according to the intention-to-treat principle, where outcomes for patients are analyzed by assigned treatment, regardless of the level of adherence. As a secondary analysis, adherence will be examined as a potential modifier of the intervention effects.

To explore whether changes in body fat (total, abdominal) mediates intervention effects on sex hormone levels, we examined the change in the measure of association pre- versus post adjustment for changes in body fat (in the linear regression model). If the adjustment attenuates the measure of association, then we consider this to be suggestive of mediation. Furthermore, the main effect of total body fat/ abdominal fat on changes in sex hormone levels will also be evaluated in the linear regression models, adjusting for the intervention assignment. This method is based on a paper of Kraemer et al86 which explains that a mediator must show a change during treatment, must correlate with the treatment assignment, and must have a main or interactive effect on the outcome.

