## Sample size calculation

Sample size calculations are based on the effect of the interventions on serum estradiol levels. The following comparisons will be made:

1) diet-induced weight loss versus combined exercise- plus diet-induced weight loss

2) diet-induced weight loss versus control

3) combined exercise- plus diet-induced weight loss versus control

The following assumptions are based on the results of the SHAPE study in women with a BMI≥25, the DIANA trial46 and the studies of McTiernan13 and Friedenreich 15:

- Mean log-transformed serum estradiol levels: 2.28 pg/ml
- Log-transformed SD: 0.44 pg/ml
- Change in diet group: -12%; pg/ml
- Change in exercise-weight loss group: -20%: pg/ml
- Power: minimally 80%
- Level of significance: 0.05 for comparison 1 and 0.025 for comparisons 2 and 3 (taking into account multiple testing).
- Drop-out: 5% in all groups
- Non-compliance/contamination: 15%

First, we calculated the sample size for the first comparison, i.e. diet-induced weight loss (n=85) versus exercise-induced weight loss (n=85), since the difference in estradiol levels between these groups is expected to be the smallest (8%). Furthermore, we think a difference of 8% will be of clinical relevance. Based on the estimated sample sizes, we calculated the number of subjects needed in the control group (n=36). The sample size of the control group can be much smaller, since the expected difference with the interventions groups is large (12% and 20%, respectively).

The sample size calculations resulted in the following estimated numbers per group, taking into account drop out and non-compliance:

- - Control group: 45
  - Diet group: 104
  - Combined exercise plus diet group: 104

The accompanying power for the other hormones to demonstrate an 8% difference between the diet and exercise group for is tabulated below:

|  | Diet vs. exercise |
| --- | --- |
| Estrone | 83% |
| Testosterone | 100% |
| SHBG | 96% |

*Abdominal fat measured by MRI*

Based on the study of Ross et al.80 (in their obese study population: mean total visceral fat was 2.3 kg SD 0.8 kg), we calculated that 81 subjects are needed to demonstrate a difference of 0.2 kg visceral fat (Alpha=0.05; Beta=0.20.) between the diet and exercise group.

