## Randomisation, blinding and treatment allocation

Randomisation takes place after the run-in phase. It will be performed by the department of data-management of the Julius Center (UMC Utrecht). We will use block randomisation, with a block size of 5, stratified by centrum and municipality.

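### As written, the main hormone comparison is an unadjusted change score on a scale chosen from the trial data; fixing the log scale and adding baseline and strata is nearly free

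*Protocol*

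**What the plan says.** Section 7.2 (Analysis) sets the form of the outcome: "Our primary and secondary endpoints will be changes in sex steroid hormones, body composition and fitness during the study". The method follows: "We will analyse the effects by linear regression analysis". Three pairwise arm comparisons are listed, by assigned group. No covariate is named for them. The mediation paragraph of the same section does name its adjustment terms (change in body fat, and intervention assignment).

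On scale, section 7.2 says: "If sex hormones are non-normally distributed, log transformations will be used for analyses". Section 7.1 applies the same condition to the tabulated values.

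Section 5.2 describes the allocation: "We will use block randomisation, with a block size of 5, stratified by centrum and municipality". Neither factor appears again in section 7.

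Section 4.4 plans estradiol on the log scale: "Mean log-transformed serum estradiol levels: 2.28 pg/ml" and "Log-transformed SD: 0.44 pg/ml". Effects are percent changes ("Change in diet group: -12%; pg/ml", and -20% in the combined group), and an 8% difference between the two intervention arms is called clinically relevant.

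**The concern.** There are two separate issues.

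**Precision.** A regression of change on arm alone treats the baseline as if it predicted the end value with a slope of exactly 1. For any correlation below 1 this leaves avoidable variance in the comparison. It also carries chance baseline imbalance into the estimate: if one arm starts higher by d, its expected change is lower by (1-r)d without any treatment effect. If centre or municipality is related to the outcome, leaving these factors out of a trial randomised within them adds further avoidable noise.

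**Scale.** The sample size presumes log estradiol, yet the analysis section lets the observed data decide. No criterion is given. It is not said whether levels, changes or residuals are inspected, and nothing keeps the primary hormones on a common scale. If estradiol passed the check, the effect would be a difference in pg/ml and no longer the relative difference on which the trial was planned. This is a matter of prespecification and interpretation, not of lost precision.

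**Working it through.** **Inputs from section 4.4.** Mean log estradiol 2.28; log SD 0.44; changes -12% and -20%; alpha 0.05 for diet versus combined and 0.025 for the comparisons with control; power 80%; 85, 85 and 36 women before inflation. The SD is that of the level. No SD of change and no baseline-to-end correlation r is given, so r is an assumption, taken here from 0.3 to 0.9.

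**Reproducing the plan's figures.** Apply the percentages to the log mean and round: 2.28 × 0.88 = 2.01 and 2.28 × 0.80 = 1.82, a difference of 0.19. Then, two-sided,

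n = 2 × [0.44 × (1.960 + 0.842) / 0.19]² = 84.2, so 85 per arm (power 80.4%).

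For diet versus control, 2.28 - 2.01 = 0.27, alpha 0.025 and 85 in the other arm give 36 controls (power 80.1%). Both stated figures are reproduced as an unadjusted two-sample comparison with SD 0.44.

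**Variances.** With equal SD s at both times:

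- change score: 2s²(1-r)
- baseline-adjusted: s²(1-r²)
- ratio, adjusted to change: (1+r)/2

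The change score has SD 0.44 only when 2(1-r) = 1, that is r = 0.5. So the stated 85 per arm matches an unadjusted change-score analysis only at that value.

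**Power at 85 per arm and n for 80% power**, difference 0.19, using power = Φ(0.19 / [SD × √(2/85)] - 1.96):

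| r (assumed) | variance ratio | power, change | power, adjusted | n per arm, change | n per arm, adjusted |
|---|---|---|---|---|---|
| 0.3 | 0.65 | 66% | 84% | 118 | 77 |
| 0.5 | 0.75 | 80% | 90% | 85 | 64 |
| 0.7 | 0.85 | 95% | 98% | 51 | 43 |
| 0.8 | 0.90 | 99.4% | 99.7% | 34 | 31 |
| 0.9 | 0.95 | about 100% | about 100% | 17 | 16 |

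Worked line at r = 0.3. Change SD = 0.44 × √1.4 = 0.521, standard error 0.0799, and 0.19/0.0799 - 1.96 = 0.42, giving 66%. Adjusted SD = 0.44 × √0.91 = 0.420, standard error 0.0644, and 0.19/0.0644 - 1.96 = 0.99, giving 84%.

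A simulation with 85 per arm (2,000 trials at each r) gave variance ratios of 0.76, 0.83, 0.90 and 0.95 at r = 0.5, 0.7, 0.8 and 0.9, in line with the formula.

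**Scale.** Assuming natural logs, the geometric mean is exp(2.28) = 9.78 pg/ml. An 8% reduction is then 0.78 pg/ml at the mean, 0.50 at one SD below (exp(1.84) = 6.30) and 1.21 at one SD above (exp(2.72) = 15.18). One difference in pg/ml cannot stand for one relative effect across these women.

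**Strata.** No between-stratum variance and no number of municipalities is given, so the gain from adding strata cannot be computed.

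**The case against.** The strongest reply is that much of this is read from silence. Section 7.2 lists no covariates but excludes none, and a statistical analysis plan that is not shown may name them. A change endpoint is also fully compatible with adjustment. Regressing change on arm and baseline gives the same arm coefficient and standard error as regressing the end value on arm and baseline; only the baseline coefficient shifts, by 1. This stands. A reader might infer that the protocol rules out baseline and strata, and it does not. What remains is that the protocol fixes the outcome as change, names adjustment terms only for the mediation models, and so describes an unadjusted main comparison.

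Second, the size depends on r, which the document does not give. At r of 0.8 to 0.9 the variance saving is only 5 to 10%. On the plan's own difference, power reaches 80% at r of 0.5 or more even without adjustment. This also stands. A reader might infer a badly underpowered trial by putting ln(0.88/0.80) = 0.095 in place of 0.19, which gives 29% rising to 37% at r = 0.5. Those figures rest on a separate question about how section 4.4 turns percentages into a log difference, and should not be charged to this analysis choice.

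Third, omitted strata make standard errors conservative only if centre or municipality predicts the outcome. The document does not show that they do.

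Fourth, the practical risk from the conditional scale may be small, since the plan already expects log values and promises geometric means if the data are non-normal. That lessens the risk but does not remove the mismatch between sections 4.4 and 7.2.

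**Conclusion.** The point holds as a worthwhile, nearly free improvement, not as an error that invalidates the trial. Its firmest part is the conditional scale: section 4.4 plans on log estradiol with percent effects, while sections 7.1 and 7.2 leave the scale to the data. That rests on the text itself.

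The precision part holds for the comparison as written, an unadjusted change score. Baseline adjustment lowers its variance by 35% at r = 0.3, 25% at 0.5, 15% at 0.7 and 5% at 0.9. The assumptions are equal SDs at the two times and a value of r that the protocol does not report. The gain matters most when r is at or below 0.5: below 0.5, 85 women per arm fall short of 80% power without adjustment (66% at r = 0.3), while adjustment gives 84% at r = 0.3. The benefit from the strata is plausible but cannot be quantified.

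**What to change.** Amend section 7.2 along these lines:

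- All sex hormones are log-transformed, with no prior check of normality. Section 7.1 is brought into line.
- Log end-of-study hormone (equivalently, log change) is regressed on arm, log baseline hormone and the randomisation strata: centre, with sparse municipalities pooled within centre by a rule set before unblinding.
- Results are given as ratios of geometric means with 95% confidence intervals.
- Body composition and fitness use the same baseline-adjusted form on their natural scale.

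The change is wording only. Hormones are measured at baseline and end of study, and the strata are known from randomisation. The cost is a few degrees of freedom and the need to write down the pooling rule.

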## Secondary objectives

To examine the effects on body(fat) composition and whether this mediates potential changes in endogenous sex hormones

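### The mediation label rests on any shrinkage of the arm coefficient, with no size, interval or binding condition; read literally it is met in about half of trials without mediation

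*Protocol*

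**What the plan says.** Section 2.2 sets the secondary objective: to examine effects on body composition and "whether this mediates potential changes in endogenous sex hormones". Section 7.2 gives the method. It opens as exploratory ("To explore whether changes in body fat (total, abdominal) mediates intervention effects on sex hormone levels") and uses linear regression with and without the change in body fat. The rule for reading the result is "If the adjustment attenuates the measure of association, then we consider this to be suggestive of mediation".

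Two further statements follow in the same paragraph. First, "the main effect of total body fat/ abdominal fat on changes in sex hormone levels will also be evaluated in the linear regression models", with adjustment for assignment. Second, the method is said to rest on a published framework under which "a mediator must show a change during treatment, must correlate with the treatment assignment, and must have a main or interactive effect on the outcome".

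The paragraph does not say that these further points must be met before the label is used, nor at what level they would be judged.

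**The concern.** The sentence that assigns the label looks only at the direction of a difference between two estimates. Such a difference is almost never exactly zero, and with no mediation its direction is settled by chance. The later statements could rescue the rule, but they are set beside it and not made conditions of it.

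Whether exercise acts on hormones through fat loss is the secondary objective, and sections 1.1 and 1.6 describe this chain as a specific interest of the investigators. There are five hormone outcomes (section 5.1.1), at least two fat measures (total and abdominal) and three arm comparisons (section 7.2), so at least 5 × 2 × 3 = 30 such results. If nothing were mediated, about 30 × 0.5 = 15 of them would be expected to carry the label on the literal reading. The results are correlated, so this is an expected count and not a prediction.

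**Working it through.** The protocol gives no error rate for this rule, so there is no figure of its own to reproduce.

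**Algebra.** Let *a* be the arm effect on fat change, *b* the effect of fat change on the hormone given arm, *c* the unadjusted and *c′* the adjusted arm coefficient. In ordinary least squares with the same women and the same other covariates in both models,

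*c* − *c′* = *a* × *b* (estimates), exactly.

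If *a* = 0 or *b* = 0, one estimated factor is scattered symmetrically around zero, so the product falls on either side of zero about equally often. Shrinkage, |*c′*| < |*c*|, then has a probability near 0.5. It departs somewhat from 0.5 when the total effect is small.

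**Inputs from section 4.4.**
- 85 evaluable women per arm for diet versus exercise; 104 per arm as the inflated number.
- "Log-transformed SD: 0.44 pg/ml", used as the residual SD.
- Mean log estradiol 2.28, changes of 12% and 20%. Total effects tried: 0.08 × 2.28 = 0.182; ln(0.88/0.80) = 0.095; 0.20 × 2.28 = 0.456; and 0. They serve only as a scale.

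**Assumed, not in the protocol.** *a* = 0, 0.5 or 1 SD of fat change; *b* = 0 or 0.15 log units per SD. Sizes are shown without sign.

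**Simulation without mediation**, 40,000 two-arm trials per row, 85 per arm unless noted:

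| *a* | *b* | Total effect | Shrinkage | Shrinkage and *b* significant at 0.05 | Shrinkage and both *a* and *b* significant at 0.05 |
|---|---|---|---|---|---|
| 0.5 | 0 | 0.182 | 49.9% | 2.4% | 2.2% |
| 0.5 (104 per arm) | 0 | 0.182 | 50.2% | 2.4% | 2.3% |
| 1 | 0 | 0.182 | 49.8% | 2.3% | 2.3% |
| 0 | 0.15 | 0.182 | 50.3% | 49.9% | 2.4% |
| 0 | 0 | 0.182 | 49.8% | 2.5% | 0.1% |
| 0.5 | 0 | 0.095 | 48.4% | 2.2% | 2.0% |
| 1 | 0 | 0.456 | 49.6% | 2.6% | 2.6% |
| 0 | 0 | 0 | 48.8% | 2.3% | 0.1% |
| 0.5 | 0 | 0 | 45.9% | 1.9% | 1.6% |
| 0 | 0.15 | 0 | 55.2% | 54.7% | 3.2% |

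**What the rows show.**
- Shrinkage alone: 46% to 55%.
- Adding a significant fat effect works when *b* = 0 but does almost nothing when *b* is real and *a* = 0. That case is possible here. Sections 1.1 and 1.5 report that fat loss goes with hormone change, and groups D and E share one weight-loss target, so their difference in fat change may be small. The protocol hopes for more fat loss in E, so *a* = 0 is a possibility and not its expectation.
- Adding both links: 0.1% to 3.2%.
- A minimum shrinkage of 10% would not control the rate: 2% to 45% over the same rows.

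**Cost in sensitivity.** In one assumed case of true mediation (*a* = 0.5 SD, *b* = 0.15, direct effect 0.10), shrinkage alone is seen in 97.6% of trials and the rule with both links in 87%.

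**Interval.** A percentile-bootstrap 95% interval for *a* × *b* excluded zero in about 4% to 6% of trials without mediation, in the scenarios checked where at most one link was real.

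**Time order.** Figure 1 puts the measurement visits, including MRI and blood, at weeks 5 and 21 only, and the Summary lists DEXA, MRI and blood sampling together in two hospital visits. Fat change and hormone change therefore span the same interval.

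**The case against.** The strongest reply is that the label sentence should not be read alone. The same paragraph evaluates the fat effect given arm and cites a framework that demands a link with assignment and an effect on outcome. If both are applied at 0.05, the false rate is a few percent at most. A reader might infer that the trial will proclaim mediation on a coin toss. The protocol does not support that, because it names the right conditions. What remains is that it does not make the label depend on them or say how they are judged.

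It can also be said that thresholds belong in the analysis plan, which is not shown. That would answer a silence, but the protocol itself states a rule for using the label, and an analysis plan that follows it would carry the same gap.

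A third reply is that the before-and-after comparison already estimates the mediated part, since the difference equals *a* × *b*. This is correct. The estimator is sound; it lacks an interval.

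A reader might extend the criticism to the neighbouring statement that "adherence will be examined as a potential modifier of the intervention effects", arguing that adherence has no meaning in the control group. The protocol does not bear this out. Section 3.1 measures dietary intake for adherence in every arm, section 3.4 monitors the controls' weight, diet and exercise, and sections 3.2 and 3.3 apply the same weekly weight-loss goal in D and E. No change to that analysis is asked for here.

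Finally, the wording is cautious and the analysis exploratory. That limits the weight of the point but does not remove it.

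**Conclusion.** The point holds in a limited form. As written, section 7.2 allows the mediation label on any shrinkage, which happens in about 46% to 55% of trials without mediation. The one additional check it describes in detail, the fat effect given arm, leaves about 50% when fat matters but the arms do not differ in fat change. The conditions that would cure this are cited but not binding.

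The percentages rest on assumed path sizes, normal errors, the planning SD as residual SD, and 85 or 104 per arm. The value near one half follows from the algebra and depends little on these choices.

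The point concerns a secondary, exploratory claim. It should be corrected before analysis but does not touch the intention-to-treat comparison of hormones.

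**What to change.** In section 7.2, keep the two regressions, fitted in the same women with the same covariates. For each comparison, hormone and fat measure, report the change in the arm coefficient as the indirect effect, with a bootstrap 95% confidence interval. Use the mediation label only if that interval excludes zero. At minimum, use it only if both the arm-to-fat and the fat-to-hormone links meet a stated level such as 0.05.

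Do not present the bootstrap as a guarantee of 5% or less: about 4% to 6% was found in the scenarios checked.

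Add a sentence that fat and hormones are measured at the same two visits, so the data cannot show which changed first.

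The cost is a few lines of code and wording, with no new data. The downside is fewer positive statements, including some missed where mediation is real (87% against 97.6% in the one case tried, under the rule requiring both links).
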